#### Regular outpatient training group

2.1.2

Patients in ROT group undergo a physical exercise workout period under the direct supervision of a physiotherapist specializing in CR. The patients will exercise on cycle ergometers (GE E-Bike Basic, Boston, MA) and treadmills (Forcelink BV, Amsterdam, The Netherlands).

A training session in ROT group consists of the following:1.Part—warm up—10 minutes2.Part—aerobic phase—60 minutes cycling on ergometers and walking on treadmill (according to predefined training heart rate set at 70%–80% heart rate reserve)3.Part—cool down—10 minutes

Training period is set to 60 minutes per one session 3 times a week for 12 weeks.

A physiotherapist will monitor each patient's heart rate and blood pressure. Measured data will be recorded on the secured external hard drive. At the end of study (after 12 weeks of training) all participants will be tested again. The main variable monitored is physical fitness assessed by CPX and SF-36 questionnaire. Physiotherapist will monitor the whole study process, and give patients of both groups proper feedback with possibility to consult any problems and difficulties related to training, technical issues, and their physical condition.

#### Outcomes

2.1.3

Main outcome is to compare physical fitness values measured at baseline and after 12 weeks in 2 groups of patients (ROT and ITG). Secondary outcomes are health related quality of life and training adherence. Health-related quality of life is measured at baseline and after 12 weeks. Training adherence is assessed in both groups during the 12 weeks of exercise period. A summary of the trial design is provided in flowchart (Fig. 1).

**Figure 1 F1:**
[figure not shown]
Flowchart of the study protocol.

## Measurements

3

### Physical fitness

3.1

Physical fitness will be measured by individual maximal CPX test with respiratory gas analysis performed on bicycle ergometer (Ergoline Ergoselect 100) using a ramp protocol. This test consists of 8 to 12 minutes cycling at 60 to 70 rpm frequency. A 12 lead ECG and blood pressure are recorded continuously during this test. Peak VO_2_ will be determined as the mean value of the last 30 seconds of exercise. Patients will be encouraged to exercise until they reach respiratory exchange ratio ≥1.10. Oxygen consumption will be measured by Metalyzer 3b (Cortex Biophysics GmbH, Leipzig, Germany).

### Health quality of life

3.2

Data related to patients’ quality of life will be assessed by an SF-36 questionnaire. The SF-36 consists of 8 scaled scores, which are the weighted sums of the questions in their section. Each scale is directly transformed into a 0 to 100 scale on the assumption that each question carries equal weight.

The 8 sections are as follows:1.Vitality2.Physical functioning3.Bodily pain4.General health perceptions5.Physical role functioning6.Emotional role functioning7.Social role functioning8.Mental health

Each patient will fill this questionnaire at baseline and after 12 weeks of training. These data will be statistically processed.

### Training adherence

3.3

Training adherence is defined as a total number of accomplished training sessions. Date will be assessed via Polar flow web application in ITG and a session attendance checklist in ROT group.

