**Discussion::**

This trial focuses on an up-to-date topic. As there have not been any similar trials in the Czech Republic yet, we expect it to bring great benefits not only for our hospital in Brno. In the long term, this method seems to be low-cost for all participants and brings a lot of benefits for those patients, who are for many reasons unable to participate in center-based CR provided by hospitals and other health care centers. Physical exercise therapy brings good results in reducing cardiovascular risk factors and improves its global impact. Thanks to its simplicity, it is expected to increase patients’ training adherence as well.

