#### Intervention training group

2.1.1

Each ITG patient will be lent a wrist sport tester (Polar M430, Kempele, Finland) which monitors heart rate and other training values—time, training mode, duration, and distance.

A training session in ITG group consists of the following:1.Part—warm up—10 minutes2.Part—aerobic phase—60 minutes walking or cycling (according to predefined training heart rate set at 70% to 80% heart rate reserve)3.Part—cool down—10 minutes

Training period is set to 60 minutes per one session 3 times a week for 12 weeks.

To know what to do and how to train at home, the first 2 training sessions will be controlled by a physiotherapist at the CR clinic in the hospital. Further training will take place in home conditions. Training data (heart rate a training values) will be recorded by the wrist sport tester. Each patient will be supposed to download the data to a Polar Flow web application (secured by login and password). Each patient will get his or her own login and password. Physiotherapists will have access to all patients’ accounts to be able to check the data. These data will be further backed up on a separate secured external hard drive, and later processed and evaluated by the trial investigator.

The great advantage of using this web application is a possibility to use it as a diary. Each patient and physiotherapist can view training history; they can follow the results to see whether they are improving or not. Physiotherapists have the role of coaches who check their patients via telephone once a week and give them feedback including recommendations, advice, and training motivation.

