### Statistical analysis

3.4

Baseline characteristics assessed from the questionnaire will be summarized using descriptive statistics. A paired *t* test will be used to find out whether there are statistically significant changes between baseline and final physical fitness values and values describing health-related quality of life. Between-group differences in physical fitness values will be evaluated by analysis of variance (ANOVA). Training adherence data will be expressed as percentage. For all statistical comparisons, the significance level will be set at *P* < .05. Analyses of all metric data (ANOVA and paired *t* test) will be processed in the statistical software Statistica 12.

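### Adherence is counted from patient-transferred watch records in the home arm and from a staff checklist in the centre arm, which puts any contrast of the two percentages at risk of differential measurement bias

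*Protocol article*

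**What the plan says.** Section 3.3 of the protocol article defines the outcome once for both arms: "Training adherence is defined as a total number of accomplished training sessions". It then names a different source for each arm: "Date will be assessed via Polar flow web application in ITG and a session attendance checklist in ROT group" (the first word evidently stands for data).

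Section 2.1.1 explains how the ITG record gets there. The watch is lent to ITG patients: "Each ITG patient will be lent a wrist sport tester (Polar M430, Kempele, Finland) which monitors heart rate and other training values". The transfer is the patient's task: "Each patient will be supposed to download the data to a Polar Flow web application". Physiotherapists can open every ITG account and telephone each patient weekly, and the first two ITG sessions are held at the clinic. No watch is described for ROT. Section 2.1.2 says that a physiotherapist monitors heart rate and blood pressure there and that measured data are stored.

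The schedule is the same in both arms: "Training period is set to 60 minutes per one session 3 times a week for 12 weeks". Both sections also list a warm-up of 10 minutes, an aerobic phase of 60 minutes and a cool-down of 10 minutes.

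Section 2.1.3 makes adherence a secondary outcome assessed in both groups. Section 3.4 says only: "Training adherence data will be expressed as percentage". The Discussion part of the abstract voices an expectation about adherence: "Thanks to its simplicity, it is expected to increase".

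**The concern.** The two sources do not capture the same behaviour in the same way. An ITG session enters the count only after the patient has worn the watch, recorded the session and transferred the file. A ROT session needs nothing from the patient after turning up. So the chance that a completed session is counted can differ by arm.

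The opposite error is also possible. An attendance list shows presence rather than completion, and a web account can hold a very short recording. The article does not say how either is to be treated.

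Adherence bears on the case for home training, and readers will set the two percentages side by side whether or not a test is attached. An apparent gain or loss for telemonitoring could then come partly or wholly from the way sessions are counted. A later analysis plan could define an accomplished session, but it cannot recover sessions that were never transferred or minutes that were never noted.

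**Working it through.** The article gives no adherence figure to reproduce. Its one power-based figure, the sample size, concerns peak VO2 and has no bearing here.

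**Inputs from the article**
- Planned sessions: 3 per week × 12 weeks = 36 in each arm (sections 2.1.1 and 2.1.2).
- ITG sessions held at the clinic: 2 (section 2.1.1), leaving 36 − 2 = 34 at home.
- Weight of one session: 1/36 = 2.8 percentage points.

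**Assumptions, because the article gives no figures**
- True adherence *a* is the same in both arms and the same for clinic and home sessions: 80%, with 70% and 90% as a range.
- Share *m* of completed home sessions never transferred: 5%, 10% or 20%.
- The 2 clinic sessions and all ROT sessions are fully captured, and no short session is credited in either arm.

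**Formula**

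Understatement of ITG adherence = *a* × 34 × *m* / 36.

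**Results at *a* = 80%**
- *m* = 5%: 0.80 × 34 × 0.05 / 36 = 1.36/36 = 3.8 points
- *m* = 10%: 0.80 × 34 × 0.10 / 36 = 2.72/36 = 7.6 points
- *m* = 20%: 0.80 × 34 × 0.20 / 36 = 5.44/36 = 15.1 points

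**Range over *a***
- At 70% and *m* = 10%: 0.70 × 3.4/36 = 6.6 points.
- At 90% and *m* = 10%: 0.90 × 3.4/36 = 8.5 points.
- If every home session were done (*a* = 100%), the figures for *m* = 5%, 10% and 20% would be 4.7, 9.4 and 18.9 points. These are ceilings for the assumed loss rates.

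**Errors in the other direction**

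Each short ITG recording credited as a session adds 2.8 points to that patient's percentage, so one of them cancels one untransferred session. Each shortened ROT session credited on the list adds the same 2.8 points in the other arm. With no transfer loss and one session rule for both arms, the artificial difference is zero. The net effect can therefore be negative, nil or positive.

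**Session length**

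The listed parts sum to 10 + 60 + 10 = 80 minutes, while the next statement gives 60 minutes per session. The wording is the same in both arms, so it creates no difference between them. It does leave open what a full session is, and a duration-based definition needs that settled.

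**The case against.** The strongest reply is that the article already contains safeguards. Staff can open every ITG account to check the data, they telephone each patient weekly, and patients may raise technical problems. Sustained and unnoticed loss of records is therefore less likely. This stands and lowers the expected size of the problem. It does not remove it, because the calls are described as feedback, advice and motivation, and nothing says that staff match uploads to sessions done or correct the count.

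A second reply is that home and centre training must draw on different sources, and that a condensed article may leave the completion threshold to the full protocol. The first half is largely right: the correctable part is the lack of a shared rule and of a reconciliation step. On the second half, the missing threshold alone would not be a finding. The differing sources and the dependence on patient transfer are stated, however, and they determine what data will exist.

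A reader might also infer several stronger things that the article does not support:
- **That the comparison is biased.** No transfer-failure rate is given and the errors can offset, so only a risk can be claimed.
- **That the plan rules shortened sessions in, or scores untransferred ones as missed.** It states neither rule. These are possible consequences of the named sources.
- **That the count in section 3.3 conflicts with the percentage in section 3.4.** With 36 planned sessions in each arm, one is a rescaling of the other.
- **That the lack of a named between-arm test for adherence is an error.** That may sit in an analysis plan not shown here.
- **That the plan predicts higher adherence at home.** The sentence in the abstract is ambiguous about its subject, and the expectation in the main Discussion covers only fitness and quality of life.

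**Conclusion.** The concern holds as a risk of differential measurement bias, of unknown size and direction, in a secondary outcome. It rests on two stated facts: the source of the count differs by arm, and the ITG source depends on an act by the patient that has no counterpart in ROT.

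The illustrative size is an understatement of ITG adherence by about 4 to 15 percentage points. That assumes 80% true adherence in both arms, 5% to 20% of home sessions untransferred, full capture elsewhere and no credited short sessions. The loss range is an assumption, and regular staff contact may keep the true rate below it. The figures show one direction only and do not estimate the net bias.

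Peak VO2 is measured by the same exercise test in both arms, so the primary outcome is unaffected. The point still deserves a change before data are collected, because the missing records cannot be rebuilt afterwards.

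**What to change.** 1. At the existing weekly call, check the sessions in the web account against those planned for the week, ask about any gap, and prompt the transfer of anything outstanding.
2. When the lent watch is returned, staff read it out and add any untransferred sessions that it still holds. How long it keeps old sessions is not stated, so the weekly check is the main safeguard.
3. Apply one duration-based definition of an accomplished session in both arms: from the watch record in ITG, and from minutes completed noted on the checklist in ROT. First reconcile the 10 + 60 + 10 minute description with the 60-minute statement in sections 2.1.1 and 2.1.2.
4. Report accomplished sessions divided by 36 for all randomised patients, including those who stop. The Methods section leaves patients excluded for serious health problems out of the final evaluation, so the adherence text should say that they are counted here.
5. Give any attendance (ROT) or any recording (ITG) as a sensitivity count.

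Do not make time in the heart-rate range a condition. Section 2.1.2 describes monitoring in ROT, not continuous session traces, and such a condition would change the outcome from sessions done to compliance with intensity.

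The cost is some protocol wording, a minutes field on the ROT checklist, one read-out per watch and slight extra record keeping. No extra visits or devices are needed.

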### Statistical analysis

3.4

Baseline characteristics assessed from the questionnaire will be summarized using descriptive statistics. A paired *t* test will be used to find out whether there are statistically significant changes between baseline and final physical fitness values and values describing health-related quality of life. Between-group differences in physical fitness values will be evaluated by analysis of variance (ANOVA). Training adherence data will be expressed as percentage. For all statistical comparisons, the significance level will be set at *P* < .05. Analyses of all metric data (ANOVA and paired *t* test) will be processed in the statistical software Statistica 12.

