## Abstract

**Background::**

Cardiovascular diseases remain the most common causes of death in the world. Instructions for secondary prevention recommend multifaceted approach in cardiovascular diseases risk management. Center-based physical exercise training is considered as an important integral part of cardiac rehabilitation (CR). Despite all recognized benefits CR brings, active interest of patients remains low in many countries, including the Czech Republic. That is why there is a need to focus on more effective patients’ participation in CR with respect to their preferences and needs. One of possible approaches is using telemonitoring guidance based on obtaining data via technological equipment during home exercise training. The aim of this study is to compare effectiveness of both center- and home-based exercise training with focus on participants’ physical fitness and quality of life.

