## Discussion

4

Despite the fact that CR brings great benefits as a prevention of cardiovascular diseases,^[26,27]^ the regular outpatient training provided by health insurances is insufficient and physical fitness of patients usually gets worse after being discharged from the hospital.^[28]^ There are a lot of reasons why these patients refuse to train on their own. Besides the financial point of view (high expenses on individual coach), there are also problems in motivation, technical, and social issues.^[29]^ The average age of patients diagnosed with CAD is 60.4 ± 10.9 years.^[24]^ These people often suffer from depression of low mood coming from their disease and are afraid to manage their physical exercises themselves.^[13]^

Fast developing technology allows us to search for new possibilities. What we need to do is to find out how to use them in modern medicine. It is the telemedicine which has already been practiced and explored in many countries. For the Czech Republic, this way of remotely controlled patient is still unexplored and unique.

Already published foreign studies show how useful, low-cost, and successful telemedicine could be,^[30,31]^ some of them talk about even better results reached by telemedicine than center-based trainings.^[32]^ To distinguish from previous studies, we decided to try a new, in our country available tool—a wrist sport tester. Data transport from patients to physiotherapist is provided via Internet connection.

The aim of this study is to monitor 2 groups of patients (ROT and ITG groups) who will undergo a 12-week training. The ROT group will be monitored under the direct supervision by a physiotherapist in a hospital; the ITG will be monitored and checked via wrist sport tester during their home-based exercise trainings. What we focus on in our study is to compare the improvement of their quality of life and physical fitness. We expect that the improvement of both variables after 12 weeks of training will be statistically significant in both ROT and ITG groups.

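### Comparing quality of life between the arms is a stated aim, but the analysis section plans only before-after tests for SF-36 and no between-arm estimate

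*Protocol article*

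**What the plan says.** **Aim.** The Abstract of the protocol article states the aim as to "compare effectiveness of both center- and home-based exercise training with focus on participants’ physical fitness and quality of life". Section 4 (Discussion) repeats it: "What we focus on in our study is to compare the improvement of their quality of life and physical fitness". The next sentence adds a within-arm expectation, that improvement "will be statistically significant in both ROT and ITG groups".

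**Status and measurement.** Section 2.1.3 (Outcomes) says: "Secondary outcomes are health related quality of life and training adherence". SF-36 is completed in both arms at baseline and at 12 weeks. Section 3.2 says: "The SF-36 consists of 8 scaled scores, which are the weighted sums of the questions in their section". It lists the eight scales and names neither a main scale nor a summary score.

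**Analysis.** Section 3.4 (Statistical analysis) plans a paired t test for "statistically significant changes between baseline and final physical fitness values and values describing health-related quality of life". Its next sentence reads "Between-group differences in physical fitness values will be evaluated by analysis of variance (ANOVA". On the significance level it says "For all statistical comparisons, the significance level will be set at" 0.05, and it mentions no adjustment.

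**The concern.** Fitness receives two analyses, a before-after test and a between-group test. Quality of life receives only the first. The stated method therefore does not match the stated aim for this outcome. This is more than a detail left to a fuller document, because section 3.4 names a method for each of the two outcomes.

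At stake is the randomized comparison. Both arms train, so neither is an untreated control. Patients enter within six months of a CAD diagnosis, know their allocation, and rate their own quality of life. A before-after change in that setting mixes the effect of training with natural recovery and with expectation. Significance in one arm but not the other would invite the reading that the arms differ. Significance in both would invite the reading that they are alike. The paired tests support neither reading.

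**Working it through.** **1. The plan's own figure.** Section 2 gives, for peak VO2, an improvement of 3.2 and an SD of 4.2 mL/kg/min, 80% power and a level of 0.05. Sidedness is not stated; two-sided is assumed, with 1:1 allocation.

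n per arm = 2(1.960 + 0.842)² × 4.2²/3.2² = 2 × 7.85 × 1.723 = 27.04, rounded up to 28, so 56 in total. This reproduces the stated 56 (the t-based solution is 28.04 per arm). The article gives no error rate or power for quality of life, so 28 per arm is used below. The planned 10% loss leaves 28 × 0.9 = 25.2, about 25 per arm.

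**2. Aim and method side by side.**

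| Outcome | Between-arm comparison an aim? | Before-after test | Between-arm test |
|---|---|---|---|
| Physical fitness | Yes (Abstract, 2.1.3, 4) | Paired t | ANOVA |
| Quality of life (SF-36) | Yes (Abstract, 4) | Paired t | None named |

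**3. Can two paired tests stand in for the missing comparison?** Suppose both arms have the same true mean change, d, in units of the SD of change, so the true between-arm difference is zero. Let p be the power of a two-sided paired t test at 0.05. The arms are independent, so the chance that exactly one is significant is 2p(1 − p). The values of d are assumptions, since the article gives no SF-36 figures.

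| d | p, n = 28 | 2p(1 − p) | p, n = 25 | 2p(1 − p) |
|---|---|---|---|---|
| 0.2 | 0.175 | 0.289 | 0.161 | 0.269 |
| 0.3 | 0.334 | 0.445 | 0.302 | 0.422 |
| 0.4 | 0.532 | 0.498 | 0.484 | 0.499 |
| 0.5 | 0.723 | 0.401 | 0.670 | 0.442 |
| 0.6 | 0.864 | 0.234 | 0.821 | 0.294 |

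For d from 0.3 to 0.5, the two arms disagree in about 40% to 50% of trials on a given scale although they do not differ. A direct between-arm test at 0.05 would be wrong in 5%.

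**4. Multiplicity (secondary point).** If no scale truly changes, the chance of at least one significant result among k independent tests is 1 − 0.95^k: for k = 8, 0.337; for k = 16 (eight scales in each arm), 0.560. A simulation of equicorrelated scales (20,000 runs) gives:

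| Assumed correlation | 8 tests | 16 tests |
|---|---|---|
| 0 | 34% | 56% |
| 0.3 | 30% | 51% |
| 0.5 | 25% | 45% |
| 0.7 | 19% | 35% |

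The rows for 0.3 to 0.7 are simulated with 28 per arm; the zero-correlation row is the formula.

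**5. What a between-arm test could detect.** With an unadjusted t test at 0.05 and 80% power, the detectable difference is 0.76 SD with 28 per arm and 0.81 SD with 25.

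**The case against.** **The within-arm expectation.** The Discussion expects significant improvement in each arm, and the paired tests serve that expectation. Section 2.1.3 ties the two-group comparison to fitness alone. Both points are correct. They explain why paired tests are there, but they do not remove the comparison of quality of life set as an aim in the Abstract and in the Discussion.

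**The closing software sentence.** Section 3.4 ends by saying that all metric data are analyzed by ANOVA and paired t test, which might be taken to cover SF-36. It names the software and the methods in use. It does not assign ANOVA to SF-36, and the sentence that does assign ANOVA names fitness.

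**Two stronger readings.** A reader might infer that the trial cannot answer its quality-of-life question. The documents do not support that: SF-36 is collected in both randomized arms at both times, so only the planned tests fall short. A reader might also infer that false positives are likely. The chance passes 50% only with 16 tests and low correlation, and every figure assumes no true change, whereas the trial expects improvement. Separate testing of each scale in each arm is itself an inference; section 3.4 does not say so, and no rule in the article lets one scale decide that quality of life improved.

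**Secondary status.** Unadjusted tests of a secondary outcome, read as exploratory, are a common and defensible choice. This stands, and it keeps multiplicity optional.

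**Conclusion.** The point holds as a mismatch between aim and method. Section 3.4, followed as written, gives no estimate of the between-arm difference in quality of life, although that comparison is a stated aim. It should be corrected.

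The cost of relying on paired tests is the 40% to 50% disagreement between arms that truly change equally. That range assumes an equal change of 0.3 to 0.5 SD and 28 patients per arm; at 0.2 and 0.6 SD it is 29% and 23%. It also supposes that someone compares the two p-values, which the plan does not prescribe but leaves as the only material for a comparison. The confounding of before-after change with recovery does not depend on these assumptions.

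Multiplicity is secondary. The range for eight tests is 19% to 34%, given no true effect and assumed correlations from 0.7 down to 0.

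**What to change.** In section 3.4, state that each SF-36 scale at 12 weeks is compared between arms by ANCOVA with the baseline score as covariate, and that the adjusted ITG minus ROT difference and its 95% CI are reported for all eight scales. Report within-arm changes as descriptive means with confidence intervals.

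Optionally, name one main scale in advance, label the scale results exploratory, or adjust. A Holm adjustment is not required and has a real price. At its first step the level is 0.05/8 = 0.00625, and a difference that has 80% power at 0.05 keeps only Φ(2.802 − 2.734) = Φ(0.068), about 53% (normal approximation).

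The cost is a few sentences and eight simple models on data already collected, with no new visits or patients. Two limits remain. ANCOVA does not remove bias from unblinded self-report. With 28 per arm, a non-significant difference will not show that the arms are alike, which is why the interval matters.

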**Methods/design::**

This randomized control trial intends to monitor cardiorespiratory health indicators and quality of life of patients diagnosed with a coronary artery disease (CAD) at the University Hospital Brno, Czech Republic. These patients will be randomly separated into 2 groups—a regular outpatient group (ROT) and an intervention training group (ITG). Both groups undergo a 12-week rehabilitation training program. The ROT group will undergo center-based exercise trainings in the hospital and receive feedback and support directly by their coach. The ITG group will be telemonitored during exercise training in their home environment via a wrist sport tester and Internet application.

All patients will be supposed to exercise at 70% to 80% of their heart rate reserve obtained from cardiopulmonary exercise test (CPX). The primary outcome is to measure and compare physical fitness values assessed at baseline and after 12 weeks of training. Physical fitness is expressed as peak oxygen uptake assessed by the CPX test. The secondary outcomes are patients, training adherence, and their quality of life.

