## Methods

2

Participants of CR-GPS project, as a single prospective randomized controlled trial, will be the patients of University Hospital (UH) Brno, Czech Republic, above the age of 18, diagnosed with CAD (angina pectoris, myocardial infarction, patients after coronary revascularization) in the last 6 months, with left ventricular ejection fraction >45%.

All eligible patients will be recommended by physiotherapists and research assistants from UH Brno. They must be clinically stable, able to undergo CPX, understand and write in Czech, and agree to participate in this project. Due to a random separation into 2 groups, all of them must have a mobile phone and free access to Internet connection.

Patients participating in CR-GPS will be further classified by cardiologist according to following criteria:No significant cardiovascular riskNo implanted cardioverter-defibrillator or pacemakerNo residual partial coronary artery stenosis requiring revascularizationNo orthopedic or neurological disability to exerciseNo mental disadvantage making cooperation impossibleNo serious oncological disease or treatment

During CR-GPS, some health problems might occur. If physical status of any participant changes significantly, he or she will be examined by the cardiologist who might change the medication. If this health problem becomes serious, this patient will be excluded from the trial. The obtained data of such patient will be further secured but not involved in final statistical evaluation.

According to Vysoký et al's study,^[24]^ number of participants calculation will be based on the improvement of peak VO_2_ 3.2 mL/kg/min with standard deviation 4.2 mL/kg/min. We will need 56 participants to reach 80% of statistical power with significance level set at *P* < .05. We count with 10% participant loss during the trial.^[25]^

At the beginning of the trial, all participants undergo baseline assessment on cycle ergometer (Ergoline Ergoselect 100, Bitz, Germany) and cardiologist will test their physical fitness through CPX. After that, they obtain a study package containing personal data questionnaire (sex, age, weight, diagnosis, pharmacological treatment), list of trial information, and informed consent form.

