Personal information will be sent to research team from UH Brno. They will be processed and backed up according to currently valid General Data Protection Regulations (GDPR). A total of 56 patients will be separated to ITG using a telemedicine assistance and ROT group with regular center-based CR. This separation will be random, done by a computerized allocation system applying an algorithm in proportion 1:1. Investigators will not be aware of the randomized matching sequence. The patient and care providers are not blinded to the intervention.

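### The between-group ANOVA of peak VO2 does not adjust for the baseline value, which loses power and leaves an avoidable error from chance baseline imbalance

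*Protocol article*

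**What the plan says.** Section 2.1.3 (Outcomes) defines the primary comparison: "Main outcome is to compare physical fitness values measured at baseline and after 12 weeks in 2 groups of patients (ROT and ITG"). The abstract says the same and specifies physical fitness as peak oxygen uptake. Section 3.4 (Statistical analysis) gives the between-group method: "Between-group differences in physical fitness values will be evaluated by analysis of variance (ANOVA"). It then lists the methods for continuous data: "Analyses of all metric data (ANOVA and paired *t* test) will be processed in the statistical software Statistica 12". Neither ANCOVA nor any covariate appears in the article. The text does not say whether the ANOVA is applied to 12-week values, to changes from baseline, or as a repeated-measures model with a group-by-time term.

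Section 2 (Methods) has all participants take the exercise test at baseline. It describes allocation only as "This separation will be random, done by a computerized allocation system applying an algorithm in proportion 1:1", with no mention of stratification by fitness. The size calculation uses an improvement of "3.2 mL/kg/min with standard deviation 4.2 mL/kg/min" and concludes: "We will need 56 participants to reach 80% of statistical power with significance level set at *P* < .05".

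**The concern.** Baseline and 12-week peak VO2 in the same patient can be expected to correlate, so the baseline value predicts much of the spread at 12 weeks. An analysis that leaves this information out, or uses it only by subtraction, has a larger standard error than it needs.

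The possible readings of the ANOVA fail in different ways:

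- **Final values.** Baseline is ignored. Each unit of chance baseline difference between the arms moves the estimated effect by r units in the same direction.
- **Change, or group by time.** With two time points the group-by-time test is the test of change scores. The baseline difference is subtracted in full, which over-corrects: each unit moves the estimate by 1 − r units in the opposite direction.

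ANCOVA removes the linear part of the imbalance in both cases. With 28 patients per arm and no stated balancing on fitness, a baseline gap that matters against a target of 3.2 mL/kg/min is quite possible.

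**Working it through.** **Inputs.** Difference 3.2, SD 4.2 mL/kg/min, 56 patients, 80% power and α 0.05 (section 2); 1:1 allocation (section 2). The article does not give r, and does not say whether 4.2 is the SD of the value or of the change. I therefore use r = 0.6 to 0.8 as an assumption, show both readings of 4.2, and assume equal SDs at the two visits.

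**The plan's own figure.** n per arm = 2(1.960 + 0.842)² × 4.2² / 3.2² = 27.04, rounded up to 28, so 56 in total. The stated size is thus a two-sided, two-group comparison with no baseline adjustment built in. Power at 28 per arm is 81% by the normal approximation and 80% by the t test. A one-sided test would need 44 patients and a paired test 16, so neither explains 56.

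**Variance ratios.** With SD σ at each visit, the error variances are:

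- final value: σ²
- change: 2σ²(1 − r)
- ANCOVA: σ²(1 − r²)

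ANCOVA / final value = 1 − r², which is 0.64, 0.51 and 0.36 at r = 0.6, 0.7 and 0.8. ANCOVA / change = (1 + r)/2, which is 0.80, 0.85 and 0.90. Both ratios are below 1 for every r between 0 and 1.

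**Power** = Φ(3.2 / (SD × √(2/n)) − 1.96), with n per arm.

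If 4.2 is the SD of change, then σ = 4.2/√(2(1 − r)) = 4.70, 5.42 and 6.64. Example at r = 0.7, n = 28: ANCOVA SD = 5.42 × √0.51 = 3.87; SE = 3.87 × √(2/28) = 1.03; 3.2/1.034 − 1.96 = 1.13; power 87%.

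| r | n per arm | Final value | Change | ANCOVA |
|---|---|---|---|---|
| 0.6 | 28 | 72% | 81% | 89% |
| 0.7 | 28 | 60% | 81% | 87% |
| 0.8 | 28 | 44% | 81% | 85% |
| 0.6 | 25 | 67% | 77% | 85% |
| 0.7 | 25 | 55% | 77% | 83% |
| 0.8 | 25 | 40% | 77% | 81% |

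The 25-per-arm rows apply the expected 10% loss to 56 (56 × 0.9 = 50.4). Simulation with 25 per arm (4,000 runs for each r) gives values within about 3 points of these: at r = 0.7, 54%, 74% and 81%.

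If 4.2 is the SD of the value itself:

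| r | n per arm | Final value | Change | ANCOVA |
|---|---|---|---|---|
| 0.6 | 28 | 81% | 89% | 95% |
| 0.7 | 28 | 81% | 96% | 98% |
| 0.8 | 28 | 81% | 99.5% | 99.7% |

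**Chance imbalance.** The SE of the baseline difference at 28 per arm is σ√(2/28). With σ = 4.2 it is 1.12 mL/kg/min (95% range ±2.2), and a gap above 1 mL/kg/min occurs with probability 2(1 − Φ(1/1.12)) = 37%. With σ = 5.42 it is 1.45, and the probability is 2(1 − Φ(1/1.45)) = 49%. At r = 0.7, a gap of 1 mL/kg/min shifts a final-value estimate by 0.7 and a change-score estimate by −0.3. Against the target of 3.2 these are 22% and 9%.

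**The case against.** The strongest reply is that the plan probably means a change-score analysis. The size calculation in section 2 and the aim in section 4 (Discussion) both speak of improvement, and section 2.1.3 names both time points. Baseline would then already be used, imbalance would be over-corrected and not left in whole, and the gain from ANCOVA would be modest. This stands: under that reading the gain at 28 per arm is about 8, 6 and 4 points at r = 0.6, 0.7 and 0.8, and about 2 points at r = 0.9.

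It also stands that the lowest power figures (40% to 60% at r = 0.7 to 0.8) arise only if 4.2 is the SD of change and final values are then analysed. If the sizing and the analysis match, the unadjusted test has about the planned 80%. Under randomisation, both ANOVA forms are unbiased with correct type I error; the imbalance is an error conditional on the baseline actually observed. The drop to 25 per arm comes from the handling of the expected loss, which is a separate matter.

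The suggestion that an unseen analysis plan might supply the model carries less weight. The article names its methods for continuous data, and ANCOVA is not among them.

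**Conclusion.** The point holds. The article fixes an unadjusted method for its primary comparison although a better one is available from data already collected. ANCOVA is more precise than every reading of the stated ANOVA for any r between 0 and 1, whichever quantity the 4.2 describes. The direction therefore rests on no contested input.

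The size does depend on assumptions: r of 0.6 to 0.8, equal SDs at the two visits, and 3.2 taken as the between-arm difference, which is how 56 reproduces. On the change-score reading that the wording favours, the benefit is about 4 to 8 power points at 28 per arm and about 4 to 9 at 25 per arm. With about 50 completers this brings power back from 77% to between 81% and 85%. On a final-value reading the benefit is larger: about 13 to 19 points if 4.2 is the SD of the value, and about 17 to 41 if it is the SD of change (28 per arm). The plan is not invalid as it stands, but the change should be made.

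**What to change.** Replace the between-group sentence in section 3.4 with:

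> The primary analysis is an ANCOVA of 12-week peak VO2 (mL/kg/min) with arm as factor and baseline peak VO2 as covariate. The adjusted ITG minus ROT difference is reported with its 95% CI and p-value.

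This also settles which outcome form and which model are primary, so that the choice cannot be made after the data are seen. The sentence that lists the methods for continuous data should then name ANCOVA as well. The cost is a change of wording in the protocol or analysis plan and one degree of freedom. No further measurement or patient is needed, and ANCOVA is a routine procedure in standard statistical software.
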